#### 16.9.4 Immunological CyTOF B/Tcell assays & and OLINK screen

**Collaborating institutions and contact persons:** [name] and [name], The [name] laboratory, Department of Microbiology and Immunology, The Global Health Vaccine Accelerator Platform (GH-VAP) program, Systems Biology/Systems Immunology Consortium, [name], USA.

**Objective:** To determine differences in cell phenotypes and protein markers in individuals with COVID19 with and without malaria, and healthy controls with no active COVID19 or malaria, and if vaccinated, at least 4 weeks previously against COVID19.

**Rationale:** Cellular activation can be profound in both COVID19 and malaria infections, leading to specific expansion or downregulation of cell populations which can have major impacts on disease progression and resolution. New technology such as CYTOF and OLINK allows simultaneous assessment of multiple cellular and protein products from small quantities of whole blood. Recent studies using CYTOF analysis from COVID19 patients described specific downregulation and immunosuppression of cellular responses, specifically those associated with CD45+ T cells. Analysis of cellular response to malaria with CYTOF has shown effects on B cell populations, specifically CD11c B cell subsets. This study provides a unique opportunity to examine the effect of co-infection on B and T cell profiles and relate these with downstream protein biomarkers which have been shown to be affected by COVID19 infection.

**Sample size:** Approximately 180 patients and 100 healthy controls

**Methods:**

**Whole Blood CyTOF Assay of Immune Phenotypes:** A small volume (270 µL) of whole blood to which a stabilizing fixative (PROT1, Smart Tube Inc., San Carlos, CA, USA) is added, to perform single-cell Mass Cytometry (CyTOF) to determine cell phenotypes and activation states in a highly comprehensive fashion, with up to 40 antibodies per sample. The [name] lab has recently developed a CyTOF panel compatible with such fixed whole blood samples and containing a number of markers of specific interest in COVID-19 research (see Table 4: CyTOF panel).

Fixed whole blood samples will be shipped on dry ice to Stanford, where they will be batched for CyTOF runs. For each batch run, samples will be thawed, washed with Lyse-Wash buffer (Smart Tube), barcoded using Pd sample barcodes (Fluidigm), and stained for cell-surface and then intracellular epitopes. They will then be treated with Ir-labeled DNA intercalator, fixed, and acquired on a Helios CyTOF instrument. At least 250,000 cell events per sample will be targeted for collection. The resulting FCS files will be normalized for intensity using EQ bead readings, de-barcoded, and analysed via both manual gating and automated methods such as FlowSOM or Citrus.

Table 4: CyTOF panel

|       |                   |      |
|-------|-------------------|------|
| 89Y   | CD66b             | HIMC |
| 113Id | CD67              | HIMC |
| 141Pr | HLA-DR            | HIMC |
| 142Nd | CD19              | DVS  |
| 143Nd | CD66a/c/e         | HIMC |
| 144Nd | CD31              | DVS  |
| 145Nd | CD4               | DVS  |
| 146Nd | BPI               | HIMC |
| 147Sm | CD20              | DVS  |
| 148Nd | CD41              | HIMC |
| 149Sm | CD11c             | HIMC |
| 150Nd | CD123             | HIMC |
| 151Eu | CD137a            | DVS  |
| 152Sm | CD45RA            | HIMC |
| 153Eu | CD45RA            | DVS  |
| 154Sm | CD3               | DVS  |
| 155Gd | CD45              | HIMC |
| 156Gd | CD38              | HIMC |
| 157Gd | CD25              | HIMC |
| 158Gd | CD33              | HIMC |
| 159Tb | GM-CSF            | DVS  |
| 160Gd | CD14              | DVS  |
| 161Dy | Ki67              | DVS  |
| 162Dy | CD69              | DVS  |
| 163Dy | TCR $\alpha\beta$ | HIMC |
| 164Dy | Arginase-1        | DVS  |
| 165Ho | CD127             | DVS  |
| 166Er | MSA43             | HIMC |
| 167Er | CD27              | DVS  |
| 168Er | CD8               | DVS  |
| 169Tm | STOM              | HIMC |
| 170Er | PD1               | HIMC |
| 171Yb | Granzyme B        | DVS  |
| 172Yb | CD15              | DVS  |
| 173Yb | Perforin          | HIMC |
| 174Yb | CD21              | HIMC |
| 175Lu | IgD               | HIMC |
| 176Yb | CD56              | DVS  |
| 208Bi | CD16              | DVS  |

**Olink Immunoassays:** Olink (Uppsala, Sweden) has developed standard immunoassay panels of 92 analytes each, using proximity extension assay technology to provide highly specific and sensitive readouts by qPCR on the Fluidigm Biomark system. Serum samples are incubated with capture antibody cocktail for the Olink Inflammation Panel (<https://www.olink.com/products/inflammation/>) and subjected to qPCR according to the manufacturer's protocol. They are transferred to a 96.96 Fluidigm array and read in the Biomark instrument. NPX values (indicative of cytokine level) are calculated by the Olink software and normalized across batches. Group-level comparisons will then be made with the normalized NPX values using univariate and multivariate regression and other possible analytical techniques.

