- a Screening for Covid-19 as part of a screening study (cross-sectional survey, source population). Screening and Day 1 evaluations may occur on the same day if the point of care antigen SARS-CoV-2 tests result is positive. This depends on the malaria status of the patient (i.e. malaria positive: Invite eligible participants to enrol in the nested malaria treatment trial on Day-0; malaria-negative: Provide the participant with the option to enrol in the COVID-19 cohort study either the same day (Day-0) or wait until the confirmatory PCR results are available on Day-1 (see e, below)). A sub-group of participants who test negative by both SARS-CoV-2 antigen RDT and malaria RDT, and are feeling well, will be invited to participate as healthy controls.
- b These evaluations will be conducted by telephone and/or text messaging
- c These evaluations will be conducted among participant enrolled in the nested malaria treatment trial only
- d Any default diagnostic swab performed by local health authorities is acceptable. Additional swabs will be taken for a SARS-CoV-2 point of care antigen test.
- e The number of days for the SARS-CoV-2 test results to become available can be longer than 1 day and may vary by site.
- f Blood sample for SARS-CoV-2, malaria diagnostics and malaria and non-malaria serology in source population (fingerpick, 250 µL dried blood spot and malaria RDT). Consenting healthy control participants will provide a single 5 mL venous blood sample for CyTOF for B and T cell markers (fixed whole blood), Olink immunoassay (plasma) and transcriptional profiling (gene expression).
- g Saliva sample (~1mL) for SARS-CoV-2 RNA and antigen detection and SARS-CoV-2 and malaria serology
- h Includes questions for the WHO Ordinal Scale for Clinical Improvement and/or modified Flu-PRO PLUS
- i Daily during the first 14 days, or until the participant is asymptomatic for two consecutive days, whichever comes last, and then on days 21, 28 and 42
- j Mid-nasal swabs for research specific molecular detection and viral load and sequencing of SARS-CoV-2 (for later batch analysis, not for patient care)

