- k Blood sample (15mL on day-1 & 28, month 3, 6, and 12; 10mL on days 3, 7, 14, 21, 42) for anti-SARS-CoV-2 antibody titre (serum), cytokine/chemokine, inflammation and disease severity biomarker panel (serum), CyTOF for B and T cell markers (fixed whole blood), transcriptomics (gene expression), malaria and non-malaria serology (serum), malaria microscopy, malaria and non-malarial pathogen detection by molecular (e.g. PCR & TaqMAN, RDT), and (in malaria positive participants) genotyping to differentiate between recrudescence or reinfection (whole blood), biochemistry (day-1 and day-28 only), full blood count for haematology (day-1 & 28 only, or when clinically indicated), host genetics (blood pellet/dried blood spots) and QuantiFERON-TB Gold In-Tube (whole blood, at enrolment or otherwise at any other timepoint after enrolment if the QuantiFERON was missed at enrolment; a repeat QuantiFERON sample will be taken at 12m for all). In children, the total volume of blood will be 2.5mL in children weighing <10kg and 5mL in children weighing 10-<15kg.
- l Blood sample for serology and for malaria microscopy and RDT. The day-21 & 42 visits are in the nested malaria treatment trial only.
- m Stool sample for detection of helminth infection, SARS-CoV-2 detection and culture.
- n Informed Consent procedures, randomization and initiation of malaria treatment may also occur on day 0 if participants test positive for malaria during the cross-sectional screening for SARS-CoV-2 by routine staff and by a SARS-CoV-2 antigen test (see d, g, above). If the SARS-CoV-2 test results turn out to be negative, the patient will complete the 3-day treatment course as assigned but will be considered a screening failure and not followed-up any further.
- o Study drug: ## denotes either artemether-lumefantrine (AL) twice daily, or pyronaridine-artesunate (PA) once daily (depending on group assignment). The first dose will be administered in the study clinic as directly observed therapy. All subsequent doses will be taken at home by the study participant if they are asked to self-isolate for home-based care, or by study/hospital staff for participants admitted to isolation wards.

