### 9.1.2 Healthy controls

In addition to enrolling those with COVID19 into the cohort, approximately 100 healthy control participants (~ 50 per country) will be invited to provide a venous blood sample (5 mL) at a single timepoint. These will be individuals identified through the screening study (cross-sectional survey, source population) and will be SARS-CoV-2 antigen RDT negative (nasal swab) and Plasmodium antigen-negative (finger prick) and will have no symptoms at the time. Where such individuals have been identified retrospectively within the previously screened population, they will be contacted and invited to repeat the rapid tests to confirm their COVID-19 and malaria-free status before providing a venous blood sample. If they have received a COVID-19 vaccine, this should be at least four weeks before the samples are taken.

Venous blood (5 mL) from those who consent will be taken into an EDTA tube and a PAXgene tube to correspond with samples from COVID-19 cohort participants.

Venous blood from healthy control participants will be used for the systems immunology component investigating T and B cell markers and for transcriptional profiling as a comparison/control group against the COVID-19-malaria negative and the COVID-19-malaria positive patients.

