#### 10.2.2 Blood samples

During the screening study (cross-sectional survey, source population) a fingerprick blood sample (about 250 µL) will be taken for malaria diagnosis by malaria RDT, malaria microscopy and a dried blood spot for malaria PCR, and for SARS-CoV-2, malaria and non-malaria serology. Approximately 100 healthy control participants (~ 50 per country) who test negative by SARS-CoV-2 antigen RDT during screening and are malaria RDT negative will have a 5 mL venous blood sample taken.

In the participants enrolled in the COVID-19 cohort study, whole blood will be stored in PAXgene Blood RNA Tubes, which inactivates and stabilises the virus, for human transcriptomics changes related to SARS-CoV-2 related and as dried blood spots (DBS, which also inactivates the virus) for Mass cytometry (CyTOF) for B and T cell markers, and parasite and host genetics related to susceptibility to respiratory illness and COVID-19 infection. The serum will be used for SARS-CoV-2, related coronaviruses and malaria serology (IgG, IgM and IgA), and cytokine and chemokine panel assays. Full blood haematology and biochemistry will be performed on day 0 and day 28. Human transcriptomics, CyTOF and cytokine and chemokine assays will be carried out on the blood samples from healthy control participants. For more details about the laboratory assays, please see sections 16.9, Appendix IX. Description of other clinical and laboratory methods, page 118.

Should funds be available, the serological assays will be extended to include antibody responses to other potential coinfections, including hepatitis, respiratory pathogens such as respiratory syncytial virus, parainfluenza, *Klebsiella pneumoniae* and parasitic infections such as schistosomiasis, and soil-transmitted helminths. Additionally, whole blood will be run for molecular diagnoses on a TaqMan array card panel to evaluate for potential viral, bacterial and parasitic coinfections and for tuberculosis Quantiferon assay (see 10.2.4, HIV testing and TB testing, below).

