## 10.4 ASSESSMENT OF IMMUNOLOGICAL ENDPOINTS

### 10.4.1 Cytokine, chemokine, and inflammatory marker profile

Serum samples collected at days 0, 1, 3, 7, 14 and 28 will be tested for cytokine and chemokines associated with cytokine storm phenomena (interleukin (IL)-2, IL-7, granulocyte colony-stimulating factor, interferon- $\gamma$  inducible protein 10, monocyte chemoattractant protein 1, macrophage inflammatory protein 1- $\alpha$ , and tumour necrosis factor- $\alpha$ ) and inflammatory markers (CRP, angiotensin 1 & 2 procalcitonin, chitinase, MxA, TREM-1). Other markers of disease severity such as D-dimer, ferritin, lactate dehydrogenase will also be considered.

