### 10.4.3 transcriptional profiling and cellular activation

Whole blood collected in EDTA will be mixed with a stabiliser (e.g. PROT1 Proteomic Stabilizer, Fisher #501351691), vortexed and frozen -80C. Serum samples will be stored at -80 for later proteomic screening for transcriptional biomarkers.

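### Olink is specified on serum in the method text but on plasma for the healthy controls, who give no serum tube, so the patient-versus-control protein comparison would mix sample type with disease

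*Protocol*

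**What the plan says.** **Olink method.** Section 16.9.4 states: "Serum samples are incubated with capture antibody cocktail for the Olink Inflammation Panel". The sentence is not limited to one group. The resulting NPX values are normalised across batches and then compared between groups. The objective of 16.9.4 covers COVID-19 patients with and without malaria and healthy controls, with about 180 patients and 100 controls.

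**Cohort proteomics.** Section 10.4.3 says: "Serum samples will be stored at -80 for later proteomic screening". It does not name Olink.

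**Healthy controls.** Footnote f of the schedule of activities (2.2.4) lists "Olink immunoassay (plasma) and transcriptional profiling (gene expression" among the uses of their single 5 mL venous sample. Section 9.1.2 says that this blood "will be taken into an EDTA tube and a PAXgene tube to correspond with samples from COVID-19 cohort participants". No serum tube is mentioned.

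**Cytokine panel.** For the cohort this is on serum throughout: "cytokine/chemokine, inflammation and disease severity biomarker panel (serum" in footnote k, "The serum will be used for SARS-CoV-2, related coronaviruses and malaria serology (IgG, IgM and IgA), and cytokine and chemokine panel assays" in 10.2.2, and "Serum samples collected at days 0, 1, 3, 7, 14 and 28 will be tested for cytokine and chemokines" in 10.4.1. Section 10.2.2 adds that cytokine and chemokine assays will also be run on the controls' blood samples, without saying whether that means serum, plasma or another matrix.

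**The concern.** The healthy controls were added so that the protein and cell results in COVID-19 patients could be read against people without active infection. That reading needs the same specimen in both groups. If patients contribute serum and controls contribute plasma, any analyte that reads differently in the two specimens will look like an effect of COVID-19. Regression adjustment cannot help, because specimen and group are then the same variable. Normalisation across batches does not address it either, and section 11.2.7 rules out any multiplicity adjustment. The purpose for which about 100 well people give venous blood would be compromised for the Olink part.

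**Working it through.** **Step 1: cross-tabulate specimen by group for Olink.**

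| | Serum | Plasma |
|---|---|---|
| COVID-19 patients (about 180) | 16.9.4 Olink method; 10.4.3 proteomic screening | not assigned to Olink anywhere |
| Healthy controls (about 100) | not possible: EDTA and PAXgene tubes only (9.1.2) | footnote f of 2.2.4 |

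Both off-diagonal cells are empty. A model with terms for group and specimen cannot estimate them separately.

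**Step 2: try the alternative reading.** Suppose the 16.9.4 sentence is generic and covers everyone. It then contradicts footnote f, and it cannot be carried out for controls with the tubes in 9.1.2. The text needs correcting on either reading.

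**Step 3: look for cohort plasma.** Section 9.2.1.2 stores serum/plasma from the enrolment draw. Section 16.9.3 speaks of paired dried blood spot, serum and plasma samples. Both suggest that cohort plasma exists. But 16.9.3 concerns a different bead assay, with a sample size listing cohort cases only, and neither section assigns plasma to Olink. The cohort EDTA blood in 10.4.3 is mixed with a stabiliser and frozen, so that text does not show a plasma aliquot.

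**Step 4: illustrate the size.** The protocol gives no figure to reproduce and no serum-plasma difference. Assume no true group difference, a pure specimen shift of d standard deviations, equal variances and a two-sided 5% z-test.

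Standard error in SD units = sqrt(1/n1 + 1/n2).
Chance of a significant result ≈ Φ(d/SE − 1.96).

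Section 11.1.2 plans about 45 malaria cases and a similar number of matched negatives per country, so 2 × 45 = 90 patients per malaria group. Section 9.1.2 sets the controls against each malaria group.

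- 100 controls v 90 patients: SE = sqrt(0.01000 + 0.01111) = 0.145. For d = 0.3, z = 2.06 and the chance is 54%. For d = 0.5, z = 3.44 and the chance is 93%.
- 100 controls v 180 pooled patients: SE = sqrt(0.01000 + 0.00556) = 0.125. For d = 0.3, z = 2.41 and the chance is 67%. For d = 0.5, z = 4.01 and the chance is 98%.

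These are per-analyte figures. The Olink panel has 92 analytes; how many would shift, and by how much, is not in the documents.

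**Step 5: mark the scope.** The immunological comparisons listed in section 4 are malaria versus no malaria (4.2) and pyronaridine-artesunate versus artemether-lumefantrine (4.3). Both lie within the cohort, where the specimen is the same. Healthy controls appear in no section 4 objective.

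**The case against.** The strongest reply is that the protocol means to match specimens. Section 9.1.2 says the control tubes correspond with cohort samples, cohort serum/plasma is stored, and the 16.9.4 wording may be no more than a generic description of the kit. On that view this is loose drafting, and the laboratory would run plasma for all. The intent is credible, and it is why the repair is probably cheap. It does not remove the point, because the only sentences that name a specimen for Olink or for cohort proteomics say serum, and controls cannot give serum.

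Three stronger readings are tempting and are not supported:

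- *That the cytokine panel is also stated to be serum against plasma.* Plasma is explicit for controls only under Olink. For their cytokine assays 10.2.2 says only blood samples; plasma is an inference from the EDTA tube, and controls also give a dried blood spot at screening. The same risk exists there, but the documents do not fix it.
- *That the malaria or treatment comparisons are biased.* They are within-cohort and unaffected.
- *That the effect could never be removed.* That is true of the data as planned. If cohort serum and plasma are both stored, running both in a subset would estimate the shift.

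It is also fair that the percentages rest on assumed shifts. They show sensitivity and do not predict what will be seen.

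**Conclusion.** The point holds for Olink. The specimen is named inconsistently, and the plan followed literally aliases specimen with group in every patient-versus-healthy-control Olink comparison. This follows from the text alone and does not depend on the assumed shifts. How much bias results is unknown: at an assumed 0.3 to 0.5 SD, the false-positive chance per analyte is about 54% to 93% against one malaria group, or 67% to 98% against all patients pooled. For the controls' cytokine assays the same problem is possible by inference, because their specimen is not named. No primary endpoint, no listed secondary endpoint and no within-cohort comparison is affected. The correction is worth making before the assays are run.

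**What to change.** 1. In 16.9.4 and 10.4.3, specify EDTA plasma for Olink in every cohort sample that will be compared with healthy controls, in line with footnote f and section 9.1.2.
2. Place patients and controls on the same plates.
3. First confirm that the cohort plasma aliquots implied by 9.2.1.2 and 16.9.3 exist for the roughly 180 selected patients. If they do not, add a serum tube for controls still to be sampled, or run paired serum and plasma in a subset to estimate the shift.
4. Keep serum for the within-cohort multiplex cytokine endpoint. Sections 2.2.3, 4.2 and 4.3 name serum for it, as do footnote k, 10.2.2 and 10.4.1, so moving it to plasma would create a new contradiction.
5. In 10.2.2, name the controls' specimen for the cytokine assays, and compare them with patients only on the same specimen in both groups.

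The cost is wording and aliquot selection if the plasma is in store. The downside is that some cohort samples may need a plasma aliquot as well as serum.

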### 16.9.5 Non-malaria serology and detection of other infection targets

**Collaborating institutions and contact persons:** [name], CDC-Kenya, Kisumu, Kenya; [name] [name], CDC, Atlanta, GA, USA.

**Objective:** To assess the influence of infection with and/or exposure to non-malarial coinfections on infection outcome on patients with COVID19 alone or with COVID19 and malaria.

**Rationale:** In both western Kenya and Burkina Faso, a large proportion of the population live with multiple active infections. It is well documented that the presence of coinfection alters immunological responses and disease outcomes. Examples include the association with increased viral load in HIV-infected individuals following malaria infection, and decreased HIV viral load and increased CD-4 counts following deworming. The overall objective of MALCOV is to characterize the immunological profiles in individuals with SARS-CoV-2 and malaria coinfection, and this will also allow analysis whether these profiles are further affected by the presence of other infections. By running an array of molecular and serological tests to detect other existing infections, we hope to:

- 1) Document common infections in individuals infected with SARS-CoV-2
- 2) Characterize immunological profiles in individuals infected with SARS-CoV-2, malaria and additional pathogens

### 3) Characterize immunological profiles coinfecting with SARS-CoV-2 infection and a non-malaria pathogen

We propose to run TaqMan array cards (TAC) developed to detect viral, bacterial, and parasitic pathogens commonly infecting individuals in western Kenya & Burkina Faso. This will require 2mL of whole blood. Samples will also be analysed in serological assays for antibody responses to hepatitis, respiratory pathogens such as respiratory syncytial virus, parainfluenza, *Klebsiella pneumoniae* and parasitic infections such as schistosomiasis and soil-transmitted helminths using the same technology as described in 16.9.2, Kinetics of SARS-CoV-2 and malaria antibodies, page 119. Additionally, stool samples will be assayed using multiplex PCR for schistosomiasis and soil-transmitted helminths, and blood for QuantiFERON-TB Gold I-Tube assay. Results will be used to describe the type and avidity of the response. Additionally, the samples will help to further validate Tetracore's multiplex bead assay (MBA) that is being developed in conjunction with the CDC. This activity is subject to further funding.

